#### *6.5.2.3.2 Selecting Patients for Potential Nested Cohort Participation*

All women meeting eligibility criteria for the retrospective cohort will be eligible for random sampling and inclusion in the nested cohort, regardless of their ART status in the national program (i.e. regardless of whether they are known to be active and in care or defaulted/ lost to follow-up). At each study site, we will enumerate a complete list of study-eligible PMTCT clients from the full retrospective cohort in chronological order of the date of their PMTCT referral/ enrolment. For relatively small enumeration lists (e.g. containing fewer than approximately 50—70 clients), all clients will be included as potential participants. For larger enumeration lists, we will randomly select every second to  $n^{\text{th}}$  PMTCT client for potential participation in the nested cohort, with the interval depending on the total number of eligible mothers at the site from which to choose at least 30 participants (e.g. if there are 80 mothers available for sampling, we will select every second entry; if there are 200 mothers available for sampling we will select every fourth entry; etc.). We will continue this selection process until we enrol at least 30 nested cohort participants at each study site. It is possible that we are unable to complete study procedures (described in detail below) on the first MIPs selected at each site. In such a case, we will continue randomly sampling from the enumeration list until we reach at least 30 consenting MIPs who have completed study procedures in fulfilment of our site-based enrolment target.

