| TOTAL                                                                                                                                                               |   | 20 | 40 |
| *Due to the highly rural and dispersed population in Neno, “high-volume” will be more than 10 pregnant women newly diagnosed in the catchment area within the past 1 year. |   |           |           |

As described in further detail below (see section 6.5.1), CFL site assessments will be conducted at about 20 purposively selected facility catchment areas where MOH PMTCT services are available and where one of the three CFL models of interest, or the SOC, are being offered.

To successfully meet our nested cohort enrolment target (accounting for missing locator information, maternal death, and other enrolment barriers), we will randomly sample at least 30 HIV-positive mothers per site from a fully enumerated list of all HIV-positive women meeting eligibility criteria, and seek to recruit a final nested sample of approximately 1,200 HIV-positive mothers and their HEIs (~30 MIPs per site x ~40 sites) from across all study sites. Based on Malawi HIV Unit program data, we anticipate that about 30 randomly selected HIV-positive mothers per site will represent a sample of between approximately 15% to 100% of all HIV-positive mothers newly enrolled into PMTCT during the full cohort period at each site, depending on PMTCT client volumes at selected facility catchment areas. This nested cohort sample size will not only allow for site-specific revised estimates of patient outcomes, but will also contribute site-level data to generate overall estimates for the full cohort for each CFL model.

To arrive at projected weights for each observation in our sampling scheme—which vary across joint strata—we have made the following assumptions: 1) at the *time of construction of the full MIP cohort*, we anticipate that approximately 73% of HIV-infected mothers will be alive and in care, with 4% documented as having transferred out, stopped ART, or died, and another 23% documented as lost to

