All estimates will be corrected based on the outcomes of sampled MIPs using methods established for general HIV programs. The weights for outcomes of interest will be derived from the product of the inverse probability of sampling for the facility catchment area ( $1/[0.25]$ ), and the inverse probability of sampling for the MIP (between  $1/[80/100]$  and  $1/[10/100]$  depending on the final enumeration cohort), and the inverse probability of participation given that a MIP was sampled ( $1/[P(R = 1 | W = w)]$ ).

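### Nested-cohort selection takes every k-th woman from a date-ordered list and stops at an enrolment count, so the chance of selection can depend on entry date; the order of approach needs to be fixed

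*Protocol*

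**What the plan says.** Protocol section 6.5.2.3.2 lists eligible women at each site "in chronological order of the date of their PMTCT referral/ enrolment". On short lists (fewer than roughly 50 to 70) every woman is a potential participant. On longer lists an interval is used, with two worked examples: "if there are 80 mothers available for sampling, we will select every second entry" and "if there are 200 mothers available for sampling we will select every fourth entry". The stopping rule is "We will continue this selection process until we enrol at least 30 nested cohort participants at each study site". If procedures cannot be completed on the first women selected, "we will continue randomly sampling from the enumeration list until we reach at least 30 consenting MIPs".

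Other sections describe the draw differently. Section 6.4.1 speaks of randomly sampling at least 30 mothers per site "from a fully enumerated list of all HIV-positive women meeting eligibility criteria". Section 6.5.2.3.8 replaces a woman who declines with the next one selected at random. The same section says that biological outcomes will be assessed for all pairs randomly selected at baseline.

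The weights in section 7.2.2.1 multiply three terms: the inverse sampling probability of the catchment area, "the inverse probability of sampling for the MIP", and the inverse probability of participation once sampled. The second term depends on the size of the enumerated list. None of the three is said to depend on entry date.

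**The concern.** Three features combine: a list sorted by calendar time, an interval shorter than the list length divided by 30, and a stop triggered by enrolments. Worked from the top, this fills the quota before the end of the list. The later a woman entered PMTCT, the smaller her chance of being selected, and when yield is high that chance is zero.

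The nested cohort exists to correct outcome estimates for everyone who entered between July 2016 and June 2017. That correction needs selection probabilities that are known and above zero. One sampling probability per site would be wrong for both early and late entrants, and no weight can recover women who could not have been drawn. Entry date is not neutral here. It governs how long a woman could be followed, when viral load is measured relative to ART start, and whether her child reaches 24 months before censoring (section 6.5.2.2).

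**Working it through.** **Yardstick.** The target difference is 8 points in 12-month retention (73% against 81%; section 6.4). A two-proportion calculation with 3:1 allocation, two-sided alpha 0.05, 80% power and continuity correction returns 298 SOC and 894 CFL mothers, as stated. The protocol's figure is reproduced, so 8 points is the right comparator.

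**Inputs from section 6.5.2.3.2.** List length N and interval k: (80, 2) and (200, 4). Stop at 30 enrolled.

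**Assumption.** Yield y, the number enrolled per woman selected, is not given. I use 0.5 to 1.0.

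**Interval against quota.** An interval spanning the list with 30 draws would be N/30: 80/30 = 2.7 and 200/30 = 6.7. The stated intervals are 2 and 4, which give 40 and 50 candidates.

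**Last position reached, working in date order.** Position = 30k/y. The list is exhausted once y ≤ 30k/N.

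| y | N = 80, k = 2 | N = 200, k = 4 |
|---|---|---|
| 1.0 | 60 (75%) | 120 (60%) |
| 0.9 | 67 (83%) | 133 (67%) |
| 0.8 | 75 (94%) | 150 (75%) |
| 0.7 | whole list | 171 (86%) |
| 0.6 | whole list | whole list |

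The exhaustion thresholds are 60/80 = 0.75 and 120/200 = 0.60. With even entry over the 12 months, 75% of the list corresponds to month 9, the end of March 2017.

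**Chance of being drawn, by quarter of the list** (simulation, 3,000 runs, random start allowed, stop at 30):

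| Case | Q1 | Q2 | Q3 | Q4 |
|---|---|---|---|---|
| N = 200, y = 1.0 | 0.25 | 0.25 | 0.10 | 0.00 |
| N = 200, y = 0.8 | 0.25 | 0.25 | 0.225 | 0.025 |
| N = 200, y = 0.6 | 0.25 | 0.25 | 0.25 | 0.20 |
| N = 80, y = 1.0 | 0.50 | 0.50 | 0.50 | 0.00 |
| N = 80, y = 0.8 | 0.50 | 0.50 | 0.50 | 0.35 |

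A random start alone does not remove the gradient.

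**Which sites.** Dividing the Table 3 ranges by sampled sites, SOC lists are 40–50, 45–60 and 30–50 women per site (strata 5, 9 and 17), all below or within the short-list limit. CFL strata 6, 7, 11, 18 and 19 (15 of 34 CFL sites) have 75–200 per site. Stratum 20 (2 sites) has 50–100. The other 17 CFL sites have 10–67.

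The stop at 30 applies to short lists too. Table 3 plans 60 women in each SOC stratum, so 180 of 230–320, or 56–78%. Worked one by one in date order, a list of 50 stops at 30/50 = 60% with y = 1 and at 37.5/50 = 75% with y = 0.8. These are the same fractions as for the 200-woman list. A list of 60 stops at 50% with y = 1.

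**Size of bias.** Assume retention changes linearly by D points from the first to the last entrant and only the first fraction f of the list is reached. The full-list mean sits at D/2 and the reached mean at fD/2, so the shift is D(1 − f)/2.
- D = 2, f = 0.9: 2 × 0.1/2 = 0.1 points.
- D = 5, f = 0.75: 5 × 0.25/2 = 0.6 points.
- D = 10, f = 0.6: 10 × 0.4/2 = 2.0 points.

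These are shifts at one affected site. Averaged over an arm the shift is smaller where other sites reach the end of their lists, and shifts in the same direction in both arms partly cancel in the contrast.

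**The case against.** The best reply is that nothing says women are approached in date order. Tying the interval to list length is how a systematic sample spans a list. Forty or 50 candidates for 30 places fits the allowance in section 6.4.1 for missing locators and deaths. Section 6.5.2.3.3 sets the route of contact by care status and next appointment, and shortfalls are made up by further random sampling. On that reading there is no truncation by date. This stands as a possible reading, but section 6.5.2.3.2 does not state it. Continuing the selection process to a count of 30, applied literally to a date-sorted list, gives the other result.

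Two stronger readings are tempting and are not supported.

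- *Late entrants are never drawn.* This holds only at high yield, and the protocol gives none. At about 60% or less (200/4) or 75% or less (80/2) the list is used up.
- *CFL results describe early entrants and SOC results the whole year.* Short lists are not taken in full: their women are potential participants under the same target of 30, and date-order working would cut SOC lists about as much. Half of the CFL sites (17 of 34) also have short lists. Thirty is a floor: stratum 11 is planned at 90/2 = 45 per site, so at 200/4 its list is exhausted at yields of 45/50 = 90% or below.

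Two further points stand. The first-stage chart review covers late entrants, so they are missing only from the correction. Section 6.1 says roll-out was stable by July 2016, which weakens one reason to expect drift.

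**Conclusion.** The stated procedure can give unequal selection probabilities by entry date, and the weighting in section 7.2.2.1 is not stated to allow for that. The protocol leaves open whether this happens, because it fixes neither a random start nor an order of approach and describes the draw differently in sections 6.4.1, 6.5.2.3.2 and 6.5.2.3.8. Those passages must be reconciled.

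The likely bias is modest: about 0.1 to 2.0 points at an affected site, for assumed linear drifts of 2 to 10 points and 60–90% of the list reached, against a target difference of 8. The documents give neither the drift nor the yield. A systematic calendar-time bias between CFL and SOC is not shown. The point is still worth acting on, because the nested cohort's purpose is correction by known probabilities and the remedy is nearly free.

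**What to change.** Before any contact, put each site's full list, short or long, into computer-generated random order. Approach women in that order until the site's target is met. Stopping at any point then leaves every entry date the same chance: at N = 200 and 80% yield, 37.5/200 = 0.19 in each quarter, in place of 0.25, 0.25, 0.225 and 0.025.

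The alternative is one systematic draw with a random start and an interval spanning the list, with every drawn entry worked to completion and no stop at 30. At high yield this could enrol more than 30 per site (up to 50 at 200/4).

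Under either version, record the number approached at each site and use it, over the list length, as the MIP sampling probability in section 7.2.2.1. Align the wording of sections 6.4.1, 6.5.2.3.2 and 6.5.2.3.8. The cost is one step per site list and a sentence in the SOP. The random-order version needs no extra participants and leaves the 298 and 894 targets unchanged.

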follow-up (LTFU) to the national PMTCT/ART program (defined by the MOH as all those who have not returned to the clinic for more than 2 months after the date when they were expected to run out of antiretrovirals and are not documented as having transferred out, stopped ART, or died); 2) mortality is 30% among HIV-infected mothers who are LTFU; and 3) a coefficient of variation of 0.15 should be adequate to obtain relatively conservative projections of precision in each joint stratum. Applying these considerations to our MIP target population, we will select between 66% and 100% of high-volume sites and about 30 MIPs at each site from across the 20 joint strata to enrol our nested cohort (**Table 3**).

**Table 3:** Illustrative sampling approach for individual mother-infant pairs at facility catchment area level.

| Joint stratum number | Total high-volume catchment areas in strata | Expected catchment areas sampled (66 - 100%) | Expected Range of number of PMTCT mothers available for sampling per joint stratum | Approximate Total Mothers sampled | Approximate Mothers with complete routine care data (.73 SOC, .80 CFLs) | Approximate Mothers Needing Tracing (0.27 SOC, 0.20 CFLs) |
|----------------------|---------------------------------------------|----------------------------------------------|------------------------------------------------------------------------------------|-----------------------------------|-------------------------------------------------------------------------|-----------------------------------------------------------|
| 1*                   | 0                                           | 0                                            | 0                                                                                  | 0                                 | 0                                                                       | 0                                                         |
| 2                    | 0                                           | 0                                            | 0                                                                                  | 0                                 | 0                                                                       | 0                                                         |

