#### **6.5.2.3.8 Community-based tracing and study activities for nested cohort participants**

For women who do not have an upcoming scheduled visit or who have been classified as “lost to follow-up” per the MOH definition, we will use all available locator information in the routine care records to contact the client by phone and/or home visit to consent the mother and conduct the questionnaire and viral load testing at a mutually agreed upon time and setting (e.g. the health facility, the client’s home, or other private location in the community). In this way, we will efficiently assess biological outcomes for *all* MIPs randomly selected at baseline.

Once the need for tracing is determined, potential participants will be sought first via telephone if a phone number is available from the treatment master card. Failing that, the potential participant will be sought in person using information available in the clinic files or master card, CFL provider files or known by HCWs or CFL providers, via study or public transportation, bicycle or on foot, as appropriate. Once found, tracers will encourage the patient to return to care. In-person tracing will be conducted with study staff trained in patient confidentiality, HIV psychosocial counselling and the protection of human research participants, leveraging existing CFL program and MOH-supported community-based tracing systems established in selected districts.

Once found, study staff and MOH CHWs and/or CFL providers will encourage the patient to return to HIV care in the national program, as is routinely done in MOH health facilities and by most CFL programs. While in the community, study tracers will obtain informed consent to proceed with study

Malawi Mother-Infant Retention Protocol v1.2, dated 3 October 2017

procedures (including DBS sample collection for mother and infant and asking the mother to complete a structured questionnaire). Study tracers will follow a standard operating procedure (SOP) developed specifically for this study that details how to identify a mutually agreed upon safe and confidential location to carry out community-based study procedures. Data will be collected from patient next-of-kin if the patient is dead. Potential participants who choose not to participate in the study will be replaced by the next randomly selected woman from the clinic enumeration list as noted under section 6.5.2.3.2 above.

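### The Protocol does not settle whether drawn women who are dead, untraced or refuse stay in the nested cohort, and its enrolment rule counts only consenting completers

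*Protocol*

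**What the plan says.** Four places in the Protocol bear on who belongs to the nested cohort.

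- **Section 6.5.2.3.2** lists eligible women "in chronological order of the date of their PMTCT referral/ enrolment", takes everyone on short lists (below about 50 to 70) and every second to n-th woman on longer ones. When procedures cannot be completed on those first selected, "we will continue randomly sampling from the enumeration list until we reach at least 30 consenting MIPs who have completed study procedures". Section 6.5.2.3.1 makes written consent, a questionnaire and blood testing the procedures in question.
- **Section 6.4.1** explains the target of at least 30 per site as "accounting for missing locator information, maternal death, and other enrolment barriers". It also assumes that "mortality is 30% among HIV-infected mothers who are LTFU".
- **Section 6.5.2.3.8** states that through tracing "we will efficiently assess biological outcomes for *all* MIPs randomly selected at baseline". It adds "Data will be collected from patient next-of-kin if the patient is dead", and then "Potential participants who choose not to participate in the study will be replaced by the next randomly selected woman from the clinic enumeration list".
- **Section 7.2.2.1** weights each pair by the site sampling probability, the pair sampling probability and "the inverse probability of participation given that a MIP was sampled". It defines retention as alive and in care among all eligible women at cohort start.

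**The concern.** The second stage exists to find out what happened to women the charts cannot account for. A quota of completers tends to select women who are alive, reachable and willing, and such women are more likely to be in care. A woman who has died or cannot be found cannot consent, answer a questionnaire or give blood. Read literally, Section 6.5.2.3.2 therefore gives her no place among the 30.

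This does not fit the promise in Section 6.5.2.3.8 to assess all pairs selected at baseline. Nor does the text say whether a death reported by next of kin counts as an ascertained outcome or only as a note on a woman who is then replaced. If participation in the Section 7.2.2.1 weight means consent and completion, a dead woman's participation probability is zero, and no inverse weight can represent her.

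At stake are the primary outcome, maternal vital status and the infant outcomes attached to these mothers. Loss is expected to be higher under SOC, so any distortion would be unequal between the groups compared.

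A smaller question concerns list order. If a chronological list is worked from the top and stopped at 30 enrolments, women who enrolled late in the period may never be reached.

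**Working it through.** **Inputs.** From Section 6.4: SOC retention 73%, target difference 8 points (so 81% under CFL), two-sided alpha 0.05, power 80%, 298 SOC and 894 CFL mothers. From Section 6.4.1: 73% in care, 4% documented as transferred, stopped or died, 23% LTFU; 30% of LTFU mothers dead. Assumptions made here: the 73/4/23 split describes SOC, and CFL keeps the same LTFU share of those not in care, so CFL LTFU = 0.19 × 23/27 = 16.2%.

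**1. The Protocol's sample size.** Pooled proportion = (0.73 + 3 × 0.81)/4 = 0.79.

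Uncorrected SOC n = [1.960 × √(0.79 × 0.21 × 4/3) + 0.842 × √(0.73 × 0.27 + 0.81 × 0.19/3)]² / 0.08² = 281.1, or 282.

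With the continuity correction, n = (281.1/4) × [1 + √(1 + 8/(281.1 × 3 × 0.08))]² = 297.5, or 298; three times that is 894. The stated figures reproduce. They treat the 1,192 women as giving unselected proportions of 73% and 81%.

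**2. Unweighted, completers only, LTFU deaths replaced, all living LTFU women traced.** Retention among completers = p / (1 − share replaced).

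- SOC: dead share 0.23 × 0.30 = 0.069; 0.73/0.931 = 78.4%.
- CFL: dead share 0.162 × 0.30 = 0.0486; 0.81/0.9514 = 85.1%.
- Contrast: 6.7 points instead of 8.0.

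The Protocol gives no untraced or refusing share, so it is varied as an assumption (still unweighted):

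| Women replaced | SOC | CFL | Contrast |
|---|---|---|---|
| LTFU dead only | 78.4% | 85.1% | 6.7 |
| LTFU dead + 20% of living LTFU | 81.2% | 87.2% | 6.0 |
| LTFU dead + 50% of living LTFU | 85.8% | 90.5% | 4.7 |
| Deaths kept; 50% of all LTFU untraced | 82.5% | 88.1% | 5.6 |

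**3. Weighted by charted care status.** Charts are abstracted for the whole cohort (Section 6.5.2.2), and care status is read from the master card for each selected woman before contact (Section 6.5.2.3.3). If no LTFU woman is really in care, reweighting completers to 73/4/23 returns 73.0%, and likewise 81.0% under CFL: a contrast of 8.0 even with every LTFU death replaced.

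Now let a share s of living LTFU women be in care elsewhere and count as retained. The true LTFU contribution in SOC is 0.23 × 0.70 × s; an LTFU sample of living women only gives 0.23 × s. The bias is 0.23 × 0.30 × s = 0.069 × s.

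- SOC: s = 20% gives 1.4 points; s = 50% gives 3.5 points.
- CFL: 0.0486 × s gives 1.0 to 2.4 points.
- The contrast shrinks by (0.069 − 0.0486) × s, about 0.4 to 1.0 point.

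This assumes that untraced living LTFU women resemble traced ones within the stratum.

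**4. Vital status.** Weighting does not help here. If next-of-kin deaths are not counted, undocumented deaths equal to 6.9% of SOC mothers and 4.9% of CFL mothers are missed, together with the outcomes of their infants.

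**5. List order.** In the Protocol's example of 200 women and every fourth entry, 50 are selected. Thirty enrolments are reached at position 30 × 4 = 120 if all enrol, or (30/0.8) × 4 = 150 if 80% enrol (assumption), leaving the last 40% or 25% unreached. In Table 3 the SOC strata 5, 9 and 17 have 80–100, 90–120 and 60–100 women over two sites each, so 30 to 60 per site. Those lists are generally short enough for everyone to be included, so the point concerns larger, mainly CFL, sites.

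**The case against.** A reader might infer that the plan removes deaths and thereby inflates SOC retention by 5.4 points. The Protocol does not support that. The 78.4% and 85.1% are raw completer proportions, and no such analysis is planned: Section 7.2.2.1 keeps all eligible women in the denominator and applies sampling and participation weights. The explicit replacement sentence in Section 6.5.2.3.8 names only those who decline, and the sentence before it collects next-of-kin data on deaths. Section 6.4.1 mentions maternal death to explain the target of at least 30, not as a replacement rule. A participation probability of zero follows only if participation means consent, which Section 7.2.2.1 does not say. The choice of covariates in that weight can properly be left to the statistical analysis plan. All of this stands, and it reduces the size considerably.

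A reader might also infer that every site's sample is truncated by date. That too goes further than the text: 30 is a minimum, the examples build in a surplus (40 of 80, 50 of 200), contact follows appointments and care status, and SOC lists are mostly taken whole. No effect of enrolment date on outcome has been shown.

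It is also true that non-response creates the bias, not replacement itself, and that fixing the draw recovers no outcome for a woman who is never found. What the objection does not remove is the conflict between a completer quota and outcomes for all selected pairs, or the open status of deaths reported by next of kin.

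**Conclusion.** The point holds as a conflict to be reconciled between Sections 6.4.1, 6.5.2.3.2, 6.5.2.3.8 and 7.2.2.1, with a bias that depends on how it is resolved. The worst unweighted reading in which only LTFU deaths are lost gives SOC 78.4% and a contrast of about 6.7 points. With weighting by charted care status, the retention bias is about 6.9 × s points in SOC (1.4 to 3.5 for s of 20% to 50%), and the contrast narrows by about 0.4 to 1.0 point. Both results assume that LTFU deaths are replaced, and both rest on the Protocol's 23% LTFU and 30% mortality, the scaled CFL LTFU of 16.2% and, for the second, a value of s that the Protocol does not give.

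The undercount of deaths, and of outcomes in those mothers' infants, is the part that weighting leaves untouched if next-of-kin reports do not count. The working gives no figure for viral suppression or infant HIV-free survival, so no size is claimed for them. Late enrollees can be missed only at larger sites where the list is worked in order.

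**What to change.** 1. Draw a fixed sample at each site, with a random start and an interval that spans the whole list.
2. Keep every drawn woman, with her ascertainment status (completed, refused, untraced, dead), in the retention and vital-status analysis, using chart, tracing and next-of-kin data. Count a confirmed death as an ascertained outcome.
3. Use replacements only to top up questionnaire and blood-sample data.
4. Base the pair sampling weights on women drawn, and estimate participation weights among living women within care status and CFL model.
5. Align the four sections with these rules.

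The cost is revised text for selection and weighting. The chart, tracing and next-of-kin data are already due to be collected. The downside is slightly more variable weights. It is best settled before drawing begins, because discarded draws may be hard to reconstruct.

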#### 6.4 Sample Size

After enumerating the full retrospective cohort, we will randomly select eligible HIV-positive women and their HEIs for our nested cohort. For this nested cohort, our sample size will be determined by a power calculation for our primary outcome of interest—maternal retention in care 12 months after ART initiation. For this calculation (*see summary in Table 2 below*), we assume that 75% of MIPs receive services from a CFL model of interest in our selected districts, and that approximately 73% of HIV-positive mothers receiving the SOC will be retained in care at 12 months post-ART initiation (based on the most recent, first quarter 2017 data from the Malawi national program). With a two-sided alpha of 0.05, we will have 80% power to detect a programmatically meaningful 8% difference in the proportion of mothers retained in care between those who do and do not receive CFL services by enrolling 894 mothers from CFL sites and 298 mothers from SOC sites into our nested cohort (for a total of 1,192 mothers). Assuming that approximately 75% of HIV-positive mothers in SOC sites will be virologically suppressed (a weighted composite of 88% suppression among the 73% of HIV-positive mothers in care and approximately 40% suppression among the 27% of HIV-positive mothers not in care), we will have 83% power to detect a 8% difference in the proportion of HIV-suppressed mothers between those who do and do not receive CFL services. Finally, assuming that we will enrol about one HEI for every mother in the nested cohort, and that 92% of all HEIs not receiving CFL services (i.e. receiving SOC) are alive and HIV-free at 12 months (based on published data that 7% of HEIs become HIV-infected by 12-months and 96% of HIV-exposed but *uninfected* infants are alive at 12 months), we will have 90%

power to detect a 5% difference in HIV-free survival between HEIs who do and do not receive CFL models of interest by recruiting 1,192 total HEIs..

| Table 2: Summary of power and sample size calculations for primary outcomes of interest. |                                 |                    |              |                                 |                                 |

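### Table 3 plans 180 standard-of-care mothers against the 298 behind the stated 80% power, and the 30-pairs-per-site rule cannot be met in Neno

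*Protocol*

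**What the plan says.** - **Power (Protocol 6.4 and Table 2).** "With a two-sided alpha of 0.05, we will have 80% power to detect a programmatically meaningful 8% difference" in retention, "by enrolling 894 mothers from CFL sites and 298 mothers from SOC sites". The SOC rate is set as "approximately 73% of HIV-positive mothers receiving the SOC will be retained in care at 12 months post-ART initiation". The same 298 and 894 carry the power for viral suppression and infant HIV-free survival.
- **Site rule (6.4.1 and 6.5.2.3.2).** Section 6.4.1 says "we will randomly sample at least 30 HIV-positive mothers per site", for about 1,200 pairs at about 40 sites. Section 6.5.2.3.2 makes this a floor on completed pairs: "we will continue randomly sampling from the enumeration list until we reach at least 30 consenting MIPs who have completed study procedures". Where a list has fewer than about 50 to 70 women, all of them are potential participants. Section 6.5.2.3.8 replaces a woman who declines with the next one on the same clinic's list.
- **Supply (6.4.1 and Table 3).** About 30 mothers per site are expected to be "between approximately 15% to 100% of all HIV-positive mothers newly enrolled into PMTCT during the full cohort period at each site". Table 3 gives, per joint stratum, the sites sampled, the range of women available and the number to be sampled. Its footnotes mark the SOC strata, oversampling in strata 10 and 11, and a lower number in stratum 16 (Neno).

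**The concern.** Table 2 and Table 3 describe the same nested cohort but do not agree on the size of the comparison group. The power calculation assumes that a quarter of mothers come from SOC sites. The sampling table delivers 15% (180 of 1,200). The smaller group dominates the variance of the comparison, so the stated 80% power for the primary outcome does not belong to the sample being planned. The power for the other two outcomes is affected in the same way.

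The site rule has a separate problem. It is a floor with no exit for a site whose list runs out, and at least one district's lists are shorter than the floor. Field staff cannot follow it there as written.

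**Working it through.** **1. Reproduce the stated sample size.** Inputs from 6.4: p1 = 0.73 (SOC), p2 = 0.81 (CFL), two-sided alpha 0.05, power 0.80, ratio k = 3. The pooled-variance formula

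n = [1.96·√(p̄(1−p̄)(1+1/k)) + 0.842·√(p1(1−p1) + p2(1−p2)/k)]² / d², with p̄ = 0.79 and d = 0.08,

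gives 281.1, so 282 SOC mothers without correction. With the continuity correction, n/4·[1 + √(1 + 2(1+1/k)/(n·d))]² gives 297.5, so 298 SOC and 3 × 298 = 894 CFL. This matches the protocol exactly, so continuity-corrected power is the like-for-like measure below.

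**2. SOC mothers in Table 3.**

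| Stratum | Areas sampled / total | Available | Planned |
|---|---|---|---|
| 5 | 2 / 2 | 80–100 | 60 |
| 9 | 2 / 2 | 90–120 | 60 |
| 17 | 2 / 2 | 60–100 | 60 |
| All SOC | 6 / 6 | 230–320 | 180 |

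- Planned shortfall: 298 − 180 = 118, or 40% of 298. CFL planned: 1,200 − 180 = 1,020.
- No SOC area is left to add. At the low end 230 < 298. At the high end 298/320 = 93% of all listed women must enrol.
- The protocol gives no participation rate. Assuming 90, 80 or 70%, a full census of SOC lists yields 207, 184 or 161 (low end) and 288, 256 or 224 (high end), all below 298.

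**3. Power at those counts.** Power = Φ[(d − c − 1.96·se0)/se1], with c = ½(1/n1 + 1/n2), se0 pooled and se1 unpooled; c = 0 for the uncorrected figure.

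- 298/894: (0.08 − 0.00224 − 1.96 × 0.02724)/0.02887 = 0.84, power 0.80 (uncorrected 0.82).
- 180/1,020: (0.08 − 0.00327 − 1.96 × 0.03246)/0.0353 = 0.37, power 0.64 (uncorrected 0.68).
- 230/894 (SOC census, low end): (0.08 − 0.00273 − 1.96 × 0.02992)/0.03208 = 0.58, power 0.72 (uncorrected 0.75).

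The same formula for the other outcomes, moving from 298/894 to 180/1,020: viral suppression (75% vs 83%) falls from 0.83 to 0.68, and infant HIV-free survival (92% vs 97%, one infant per mother) from 0.90 to 0.79. All these figures ignore clustering by site and the sampling weights.

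**4. Site rule against Table 3.** In each of these strata every high-volume area is already sampled.

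| Stratum | Sites | Available | Per site | Planned | Planned as % of supply |
|---|---|---|---|---|---|
| 16 (Neno) | 5 | 50–100 | 10–20 | 90 | 180–90% |
| 10 | 4 | 100–200 | 25–50 | 150 | 150–75% |
| 8 | 2 | 60–100 | 30–50 | 60 | 100–60% |
| 17 | 2 | 60–100 | 30–50 | 60 | 100–60% |

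In Neno, 30 per site needs 5 × 30 = 150 pairs from 50 to 100 women, which is impossible at either end. In stratum 10 it needs 120 from 100 at the low end. In strata 8 and 17 at the low end it needs every listed woman.

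**5. Total.** Table 3's columns add as printed (40 sites, 2,740–3,720 available, 1,200 sampled). Capping each stratum at its low-end supply removes 50 (stratum 10) and 40 (stratum 16): 1,200 − 90 = 1,110. At the high end no stratum exceeds supply and the total stays at 1,200. With 90, 80 or 70% participation (assumed), the totals are 1,083, 1,056 or 1,025 at the low end and 1,200, 1,190 or 1,170 at the high end.

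**The case against.** - **Table 3 is labelled illustrative, with approximate and expected numbers.** True, but it is the only allocation given. The gap of 118 SOC mothers is too large to be rounding, and it exists at the planned numbers whatever the availability turns out to be.
- **Thirty is a minimum, and short lists are taken in full as potential participants.** SOC lists average 30 to 60 women per site, so the SOC count could exceed 180. This stands as far as it goes. But a complete census gives only 230 to 320, so it reaches 298 only near the top of the range with 93% enrolment. For Neno the short-list clause does not help, because it widens who is approached and leaves the floor of 30 completed pairs in place.
- **The Neno reduction is disclosed and offset.** Also true. Stratum 16 is 60 below 30 per site (90 vs 150), and strata 10 and 11 are each 30 above it, so 1,200 is a deliberate reallocation. The footnote still contradicts the site rule, and half the offset sits in stratum 10, which cannot supply it at its low end.
- **Deaths need not lose the outcome.** Section 6.5.2.3.8 provides for next-of-kin data, which softens the lack of slack in strata 8 and 17. It does not cover refusals or missing locators.
- **A reader might infer that 1,200 pairs cannot be reached.** The protocol does not support that. The allocation fits at high availability, overall supply is at least 2,740, and large strata such as 6, 11 and 19 have room above 30 per site.
- **A reader might also blame strata 8, 10 and 16 for the SOC gap.** They are CFL strata. Even capped at low-end supply, CFL keeps 1,110 − 180 = 930 pairs, above 894.

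**Conclusion.** The point holds in two parts. First, the sample in Table 3 (180 SOC, 1,020 CFL) is not the sample in Table 2 (298, 894). On the protocol's own method, power for the primary outcome is about 0.64, not 0.80. A full SOC census at low availability, with 894 CFL mothers, would raise it to about 0.72. Second, the floor of 30 completed pairs per site cannot be met in Neno at either end of the range or in stratum 10 at the low end, and strata 8 and 17 can meet it at the low end only with full participation.

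The total of 1,200 is a risk at low availability, not an impossibility. These conclusions rest on Table 3's availability ranges and on the 73% and 81% of section 6.4. The participation rates are assumptions. The SOC mismatch and the Neno conflict do not depend on them.

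**What to change.** 1. In section 6.4 and Table 2, replace 298 and 894 with expected SOC and CFL counts built from Table 3. For each stratum take the smaller of the target and availability times a stated participation rate, at both ends of the range. Restate the power for all three outcomes at those counts.
2. Say whether sites with short lists stop at 30 or enrol every willing woman. This decides whether the SOC count is about 180 or 230 to 320 times participation.
3. In 6.4.1 and 6.5.2.3.2, change the site rule to 30, or all eligible women if fewer.
4. Cap the Table 3 targets for strata 10 and 16 at availability, and show the total as a range.

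The cost is a revised table and a less favourable power statement. No added enrolment is needed.
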